## Abstract

**Background:**

Androgen deprivation therapy (ADT) is the mainstay therapy for men with prostate cancer. However, there are musculoskeletal side effects from ADT that increase the risk for osteoporosis and fracture, and can compromise the quality of life of these individuals. The objectives of this study are to determine the efficacy of a home-based walking exercise program in promoting bone health, physical function and quality of life in men with prostate cancer receiving ADT.

**Methods/Design:**

A 12-month prospective, single-blinded, randomized controlled trial will be conducted to compare the Exercise Group with the Control Group. Sixty men with prostate cancer who will be starting ADT will be recruited and randomly assigned to one of the two groups: the Exercise Group will receive instructions in setting up an individualized 12-month home-based walking exercise program, while the Control Group will receive standard medical advice from the attending physician. A number of outcome measures will be used to assess bone health, physical function, and health-related quality of life. At baseline and 12 months, bone health will be assessed using dual-energy X-ray absorptiometry. At baseline and every 3 months up to 12 months, physical function will be evaluated using the Functional Assessment of Chronic Illness Therapy - Fatigue Scale, Activities-specific Balance Confidence Scale, Short Physical Performance Battery, and Six-Minute Walk Test; and health-related quality of life will be assessed using the Functional Assessment of Cancer Therapy Prostate Module and the Medical Outcomes Study 12-item Short Form Health Survey Version 2. A mixed multiple analysis of variance will be used to analyze the data.

**Discussion:**

Musculoskeletal health management remains a challenge in men with prostate cancer receiving ADT. This study addresses this issue by designing a simple and accessible home-based walking exercise program that will potentially have significant impact on reducing the risk of fracture, promoting physical function, and ultimately improving the health-related quality of life in men with prostate cancer receiving ADT.

**Trial registration:**

ClinicalTrials.gov: NCT00834392.

## Background

Prostate cancer is the most commonly diagnosed cancer among men in North America, excluding non-melanoma skin cancer. There are currently 25,500 men in Canada [1] and over 2.3 million men in the United States who have prostate cancer [2]. Despite apparently localized and hence curable disease at presentation, more than one-third of men with prostate cancer will develop recurrent disease. Androgen deprivation therapy (ADT), accomplished by bilateral orchiectomy or the use of a luteinizing hormone-releasing hormone (LHRH) agonist, is the mainstay therapy for recurrent and/or metastatic prostate cancer. The duration of response to ADT using an LHRH agonist ranges from 12 to 18 months, with 20% of patients having a complete prostate specific antigen (PSA) response at 5 years [3]. However, there are a number of side effects of ADT that negatively impact the health-related quality of life in these men. The side effects of such treatment include osteoporosis, [4,5] increased fracture risk, [6-8] poorer quality of life with decline in physical function, [9,10] fatigue, decline in muscle mass, increased fat mass, weight gain, [11,12] reduced psychosocial and cognitive functions [13,14]. Osteoporosis and physical function decline are of particular concern as these are factors that are closely related to risks of falls and fractures in older men [15-18].

Exercise is an easily accessible lifestyle intervention that may have significant positive impact on the quality of life in men with prostate cancer. A number of studies have already shown that exercise improves the quality of life and even survivorship in women with breast cancer [19,20]. However, there are few studies investigating the effects of exercise on bone health and physical function in men with prostate cancer. Walking has been shown to have beneficial effects on bone metabolism in post-menopausal women [21]. We speculate that walking may have a similar effect on bone metabolism in men with prostate cancer receiving ADT. In addition, a study showed that short-term supervised, rigorous resistance exercise could reduce fatigue and improve muscular fitness, and improve some aspects of quality of life in men with prostate cancer receiving ADT [22]. Therefore, it is imperative to explore other forms of exercise that can achieve similar results as resistance exercise, but are more accessible and can be readily incorporated into the long-term lifestyle of men with prostate cancer. The purpose of this study is to determine the efficacy of a home-based walking exercise program in promoting bone health, physical function and quality of life in men with prostate cancer receiving ADT.

## Methods/Design

A 12-month prospective, single-blinded, randomized controlled pilot study will be conducted to compare an Exercise Group with a Control Group. The study will be conducted in the Department of Physical Therapy in the Faculty of Medicine at the University of Manitoba. Patient recruitment will be conducted through Cancer Care Manitoba, with baseline and follow-up sessions at the Department of Physical Therapy at University of Manitoba. The University of Manitoba Research Ethics Board has approved the study protocol (Ethics Reference # H2008:035), which is also in compliance with the Helsinki Declaration.

### Participants

#### Inclusion criteria

Patients will be included in the study if they are men aged 50 years or older, diagnosed with adenocarcinoma prostate cancer, and who will initiate and receive continuous ADT (LHRH agonist alone or in combination with another anti-androgen) for at least 12 months after recruitment. Patients will be required to provide written informed consent to participate in the study.

#### Exclusion criteria

Patients will be excluded from the study if they have severe cardiac disease (New York Heart Association class III or greater), angina, pre-existing osteoporosis with T-score at or below -2.5, stable bone lesion, uncontrolled hypertension (blood pressure > 160/95 mm Hg), moderate to severe aortic stenosis, acute illness or fever, uncontrolled atrial or ventricular dysrhythmias, uncontrolled sinus tachycardia (> 120 beats per minute), third-degree atrio-ventricular heart block, active pericarditis or myocarditis, recent pulmonary embolism, deep vein thrombosis, uncontrolled diabetes, uncontrolled pain, cognitive impairment, history of falls due to balance impairment or loss of consciousness, severe neuromusculoskeletal conditions that limit their ability to perform walking exercise (including ataxia, peripheral or sensory neuropathy, unstable bone lesion, severe arthritis, pathological lower limb fractures within 6 months, lower limb amputation).

#### Recruitment

A total of 60 patients will be consecutively recruited during the initial 3-months of the study from office visits at Cancer Care Manitoba. The attending physician will screen the patients for inclusion criteria (men aged 50 or older), diagnosed with prostate adenocarcinoma, will initiate and receive continuous ADT (LHRH alone or in combination with another anti-androgen for at least 12 months). If the patients meet the preliminary inclusion criteria, the physician will refer them to a clinical research nurse who will confirm that all inclusion and exclusion criteria are met, explain the study protocol, provide information sheet, and obtain written informed consent from any patients who would like to participate in the study. The clinical research nurse will provide a graduate research assistant (GRA1) with the signed consent forms and contact information of the patients who have agreed to participate in the study.

### Assessment sessions

Each participant will attend a total of five assessment sessions: one baseline, and four follow-up sessions at 3, 6, 9, and 12 months after ADT initiation. The Exercise Group will complete telephone survey between follow-up sessions.

### Baseline assessment session

GRA1 will contact the participants to schedule a baseline assessment. GRA1 will collect the socio-demographic and clinical characteristics, followed by primary outcome (HRQOL and physical function) and secondary outcome variables (physical fitness, psychosocial-cognitive functions, and physical activity).

GRA2 (another graduate research assistant) will provide each participant with a pedometer to monitor his ambulatory activities. The participants will be instructed to wear the pedometer during waking hours, except while bathing or swimming. The pedometer will be worn on a waistband, at or slightly anterior to the mid-axillary line. The exact location will be determined by a 50-step trial walk, and the placement that yields the least percentage error in step counts will be used for the individual's daily application. Pedometer daily logs, self-addressed envelopes, and extra batteries will be provided to all participants. At the end of each day, participants will record the date, total daily time wearing the pedometer, and the number of daily steps taken, and then reset the pedometer to zero. Every four weeks, GRA2, will call the participants to remind them to return their pedometer daily logs by mail in the self-addressed envelopes.

#### Randomization of group assignment

GRA1 will be blinded to the group assignments of the participants. Therefore, after the baseline assessment and pedometer instruction, GRA2 will be responsible for the randomized group assignment. GRA2 will assign the participant the first available number from a randomly generated list consisting of "1" and "2". Number "1" is designated as the Exercise Group that will receive instructions in setting up an individualized 12-month home-based walking exercise program in addition to their daily activities. Number "2" is designated as the Control Group that will be advised to perform daily activities as usual and follow the standard medical advice from their attending physician.

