#### Exercise group protocol

GRA2 will assess the baseline health and fitness of the participants of the exercise group by using an exercise screening form that includes the revised Physical Activity Readiness Questionnaire (PAR-Q), [23] and other screen questions for exercise contraindications and precautions. If any exercise contraindication is identified (e.g. shortness of breath, severe headache, sudden onset of numbness or weakness), the participant will be excluded from the study and referred to their family physician for investigation. If any exercise precautions is identified (e.g. fever, severe cachexia, extreme fatigue, sickness or bone pain), high-intensity or high-impact exercise will be initially avoided. If severe nausea or calf pain is present, the participants will be advised to consult their family physician for further investigation and clearance prior to beginning the exercise program.

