
### Between follow-up sessions

For the first 20 weeks, GRA2 will call the Exercise Group participants every two weeks to monitor their safety, adherence, and progress using a short, structured phone survey. The results of the phone survey will be used to guide the adjustments/progression of the structured exercise and step counts protocols. After 20 weeks, GRA2 will conduct the phone survey every four weeks. In addition, the participants will return their exercise daily logs every four weeks.

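### The person who delivers the exercise programme also allocates from a list with known codes, with no described step hiding upcoming assignments, and can later exclude men from the Exercise Group only

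*Protocol article*

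**What the plan says.** All references are to the protocol article.

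- **Recruitment.** The attending physician makes a preliminary check and refers the man to a "clinical research nurse who will confirm that all inclusion and exclusion criteria are met". The same nurse is to "obtain written informed consent from any patients who would like to participate in the study".
- **Baseline assessment session.** GRA1 schedules the session and takes the baseline measurements. Then "GRA2 (another graduate research assistant) will provide each participant with a pedometer to monitor his ambulatory activities"; its placement is settled with a 50-step trial walk.
- **Randomization of group assignment.** GRA1 is kept blind to group. For that reason, "after the baseline assessment and pedometer instruction, GRA2 will be responsible for the randomized group assignment". The mechanism is that "GRA2 will assign the participant the first available number from a randomly generated list" made up of 1s and 2s. The codes are fixed: 1 "is designated as the Exercise Group that will receive instructions in setting up an individualized 12-month home-based walking exercise program", and 2 is the Control Group.
- **Exercise group protocol.** "GRA2 will assess the baseline health and fitness of the participants of the exercise group by using an exercise screening form". A contraindication leads to exclusion from the study and referral to the family physician. GRA2 also teaches the stretching routine.
- **Between follow-up sessions.** For the first 20 weeks "GRA2 will call the Exercise Group participants every two weeks to monitor their safety, adherence, and progress", and the results guide progression.

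**The concern.** Randomisation prevents selection bias only if nobody who can affect a man's entry or its timing knows his assignment before he is irrevocably registered. Here one person works the list, knows what the codes mean, has already seen the man walk, and has a natural interest in how the Exercise Group fares. The reason given for this arrangement is to keep GRA1 blind. That guards the measurement of outcomes but does nothing for the allocation itself.

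The exercise screen raises a second, related problem. It is applied after allocation and in one arm only, by someone who knows the group. Men with contraindications leave the Exercise Group, while comparable men stay in the Control Group. The groups then differ for a reason other than the intervention.

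The outcomes at stake include primary ones that depend on fitness, notably the 6-Minute Walk Test and the Short Physical Performance Battery.

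**Working it through.** The article gives no figure on this point to reproduce: no alpha, power, effect size or allocation ratio. The check is a comparison of the sections in the order in which a man meets them.

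| Step | Who | Before or after allocation | Arms |
|---|---|---|---|
| Preliminary eligibility | Attending physician | Before | Both |
| Full eligibility and consent | Research nurse | Before | Both |
| Scheduling and baseline measures | GRA1 (blind) | Before | Both |
| Pedometer issue and instruction | GRA2 | Before | Both |
| Allocation from the list | GRA2 | At allocation | Both |
| Exercise screen, with possible exclusion | GRA2 | After | Exercise only |
| Teaching and progress calls | GRA2 | After | Exercise only |
| Follow-up measures | GRA1 (blind) | After | Both |

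**Allocation.**
1. GRA2 takes the next entry from the list, and the codes are not masked. Stated.
2. GRA2 has contact with every man before taking that entry. Stated.
3. GRA2 delivers the intervention. Stated.
4. Something prevents GRA2 from seeing the next entry. Not stated. The article does not say who generates or keeps the list, or whether envelopes or a central system are used.
5. What GRA2 could affect with foreknowledge. Not eligibility, consent or baseline scheduling, which belong to others. What remains is the moment at which a man takes his number once baseline and pedometer instruction are done. Recruitment of 60 men in 3 months is about 60/13 = 4.6 a week, so two men could plausibly be at that stage together, although the article describes no waiting pool.

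**Exclusion after allocation.** This does not depend on foreknowledge. Let p be the share of men who would fail the screen, the same in both arms, and d the amount by which their mean change over 12 months is worse than that of the other men. Suppose exercise has no effect and the other men change by m on average.
- Exercise Group after exclusions: mean change = m.
- Control Group, unscreened: mean change = (1 − p)m + p(m − d) = m − pd.
- Spurious difference in favour of exercise: m − (m − pd) = pd.

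Neither p nor d is given, so no value follows. The sign is favourable to exercise if men with contraindications decline faster. The difference is one of change, so it enters the planned Group × Time test directly.

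**The case against.** The strongest reply is that a journal article condenses the full protocol, and that custody of the list and use of envelopes are the kind of detail left out. That stands as far as it goes: the silence does not show that the list is open. What the article does state is the division of roles, and that division puts the list in the interventionist's hands.

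The second reply is that GRA2 has little leverage. Men are recruited consecutively, the nurse settles eligibility and consent, GRA1 schedules baseline, and measurement precedes allocation. This also stands. The usual harm from foreknowledge, selective enrolment, would need GRA2 to pass information to the physician or nurse. Only order and timing are left.

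Three stronger readings are tempting and are not supported:

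- *That the whole list can be read in advance.* The article does not say that GRA2 sees beyond the next entry, or that assignments are unconcealed as a matter of fact.
- *That GRA2 screens each man before allocating him.* The form applies to men already in the Exercise Group. The one-arm exclusion is a defect of its own and would exist under perfect concealment; it is not evidence that concealment fails.
- *That steering would produce a known bias in the result.* Assume 30 men per arm. Each steered pair of men 1 SD apart in fitness shifts the expected group difference by 1/30 SD relative to random order, so three such pairs give 3/30 = 0.10 SD. The number of pairs is invented. A fixed fitness difference is also present at baseline and largely cancels from the Group × Time interaction; only a difference in change would survive.

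The possibility of unequal group sizes is a separate matter. The article does not say whether the list is restricted, and imbalance is not a failure of concealment.

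**Conclusion.** The point holds in two limited parts. First, the article assigns the list to the person who has met each man and will coach half of the trial, and describes nothing that hides upcoming assignments from that person. Concealment is therefore not assured on the text, and the order or timing of allocation could be influenced. Second, the article prescribes exclusion from the study after allocation, in one arm, by the same unblinded person. This second part is explicit and needs no inference.

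No size can be given for either. The first depends on how the list is actually kept and on how often men overlap. The second depends on how many men fail the screen and how differently they would have changed. If the full protocol already provides for concealment, the first part reduces to one clarifying sentence; the second part remains. This should be changed rather than being fatal to the design. It matters because a breach of concealment cannot be repaired in the analysis, and the correction is inexpensive.

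**What to change.** - Have a person with no participant contact generate the list and hold it.
- Move the existing exercise screen, with its content unchanged, to before allocation, and apply it to every man.
- Release each assignment through sequentially numbered opaque sealed envelopes or a locked electronic form, only once consent, baseline assessment and the screen are complete and the man's number and the date are recorded. GRA2 may still open the envelope or form.
- State these steps in the randomisation section, and reconcile the exercise-group section with them so that the screen no longer removes allocated men from one arm.

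The cost is a little administrative time, the extra work of screening Control men, and a short change of wording. Blocking the list or stratifying it by treatment intent may be worth considering on other grounds but would not address this point.

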#### Exercise group protocol

GRA2 will assess the baseline health and fitness of the participants of the exercise group by using an exercise screening form that includes the revised Physical Activity Readiness Questionnaire (PAR-Q), [23] and other screen questions for exercise contraindications and precautions. If any exercise contraindication is identified (e.g. shortness of breath, severe headache, sudden onset of numbness or weakness), the participant will be excluded from the study and referred to their family physician for investigation. If any exercise precautions is identified (e.g. fever, severe cachexia, extreme fatigue, sickness or bone pain), high-intensity or high-impact exercise will be initially avoided. If severe nausea or calf pain is present, the participants will be advised to consult their family physician for further investigation and clearance prior to beginning the exercise program.

The Exercise Group will follow a walking exercise program that comprises a progressive structured exercise protocol and progressive target daily step counts. The structured exercise protocol will initially begin with a 10-minute walking session, 3 sessions per week. The Exercise Group participants will be instructed to perform a 5-minute warm-up period by walking slowly prior to the 10-minute walking session. There will also be a 5-minute cool-down period by walking slowly, followed by a stretching routine after the 10-minute walking session. The stretching instruction sheet will be provided to the participants. GRA2 will also educate and demonstrate to the participants how the stretches are to be done. During the warm-up/cool-down periods, the participants will maintain an exertion level between 7.5 and 8 on the Borg Scale of Ratings of Perceived Exertion (RPE) [24] (i.e., extremely light level of exertion). During the 10-minute walking session, the participants will gradually increase the walking speeds until they attain and maintain an RPE level between 9 and 13 (i.e., very light to light exertion) according to their baseline physical activity level (sedentary, moderately active, or active) as reported on their self-reported physical activity questionnaire. Sedentary individuals will walk at RPE level 9 (very light exertion), moderately active individuals will walk at RPE level 11 (light exertion), and active individuals will exercise at RPE level 13 (somewhat hard exertion). Each participant's exercise level will be progressed every two week, first in frequency (1-day increment), then duration (5-minute increment), and lastly RPE level. Based on the set progression protocol, the Exercise Group participants will be performing five walking exercise sessions per week, 30 minutes walking per session, and will attain RPE level 15 (heavy exertion) during the walking session by around 18 to 20 weeks. This level of exercise protocol will be maintained for the rest of the study period. The participants are instructed to record the date, start time, exercise duration and maximum RPE attained during each session in an exercise daily log. The participants will also be encouraged to walk at their chosen pace at times outside their structured exercise protocol so as to achieve their assigned target daily step counts. The initial target will be set at 5,000 steps for sedentary individuals, 6000 steps for moderately active individuals, and 7,000 steps for active individuals. The target daily step counts will be progressed every two weeks (1000-steps increment) up to a maximum daily target of 10,000 steps. The participants will be counseled on the warning symptoms of impending cardiovascular events including chest pain or discomfort, shortness of breath, dizziness, severe headache, sudden onset of numbness or weakness, or calf pain suggestive of deep vein thrombosis. They will be strongly advised to discontinue the exercise program and report these symptoms to their attending physician and GRA2 immediately. An exercise advice and instructions sheet will be provided to the Exercise Group participants.

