### Statistical analysis

#### Primary outcome variables

A mixed multiple analysis of variance (MANOVA) (Group X Time) will be conducted to determine if there is a significant interaction between the between- group (Group) and within-group (Time) comparisons for:

*Bone health *(bone mineral density) at baseline and 12-month follow-up session;

*HRQOL *(FACT-P and SF-36), and *physical function *(FACT-Fatigue, ABC, SPPB, and 6MWT) at baseline, 3, 6, 9, and 12-month follow-up sessions.

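### The exercise-safety screen is applied after randomisation, to the Exercise Group only, and men who fail it leave the study; this can bias the Group x Time comparison by an amount and in a direction that the plan does not fix.

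*Protocol article*

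**What the plan says.** All references are to the protocol article. The order of events is as follows.

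- **Recruitment.** The attending physician refers men to "a clinical research nurse who will confirm that all inclusion and exclusion criteria are met" and who then takes consent. This check covers every man.
- **Baseline assessment session.** The first research assistant (GRA1, kept blind to allocation) collects the outcomes. GRA2 fits the pedometer and gives instruction to every man.
- **Randomization of group assignment.** "after the baseline assessment and pedometer instruction, GRA2 will be responsible for the randomized group assignment". The other arm is described as a "Control Group that will be advised to perform daily activities as usual and follow the standard medical advice from their attending physician". Nothing further is required of these men at this point.
- **Exercise group protocol.** For men allocated to walking, this section opens with a screen: "GRA2 will assess the baseline health and fitness of the participants of the exercise group by using an exercise screening form". The form contains the readiness questionnaire and questions on contraindications and precautions. The contraindications are given as examples. When one is present, "the participant will be excluded from the study and referred to their family physician for investigation".
- **Statistical analysis, primary outcome variables.** The planned test reads: "A mixed multiple analysis of variance (MANOVA) (Group X Time) will be conducted to determine if there is a significant interaction".

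No section gives this form, or a matching exclusion, to the Control Group. No section says that men excluded by it are followed up or analysed as randomised.

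**The concern.** Randomisation makes two groups comparable only if the men who were randomised are kept. Here a rule removes men from one arm on the basis of symptoms, and men with the same symptoms remain in the other. The example triggers (shortness of breath, severe headache, sudden numbness or weakness) are plausibly related to the fatigue, physical performance, walking and quality-of-life outcomes. The men who remain in the Exercise Group are therefore a selected subset, compared with an unselected Control Group.

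The person who applies the rule has just made the allocation and knows it. Because the list of contraindications is open, some judgement is left to that person. GRA1's blinding protects the measurement of outcomes, but not the decision about who is left to be measured.

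This is a stated procedure and not a missing detail, so an analysis plan that is not shown does not remove it.

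**Working it through.** **Order and scope.** The screen is addressed to participants of the Exercise Group. That group exists only once GRA2 has allocated, so the screen follows randomisation. It applies to one arm, and its stated consequence is removal from the study, not merely from the walking programme.

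**Figures in the plan.** The article gives no failure rate, effect size, SD, significance level or power, so there is no figure to reproduce. What follows is an illustration on assumed inputs.

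**Inputs**
- Total randomised: 60 (Abstract, Methods/Design: "Sixty men with prostate cancer who will be starting ADT will be recruited and randomly assigned to one of the two groups"). Assumed 30 per arm, because the allocation ratio is not stated.
- *f*: share of men, in either arm, who would fail the form. Assumed 5% and 10%.
- *D*: how much worse the failing men would change from baseline than the passing men, in SD of the change. Assumed 0.5 and 1.0.
- Two-sided 0.05 test of a single change score, normal approximation. This simplifies the planned multivariate test.

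**Shift when walking has no effect.** After the exclusion, the Exercise Group contains only passing men, with mean change μ. The Control Group contains both kinds, with mean change (1 − *f*)μ + *f*(μ − *D*) = μ − *fD*. The difference between arms is therefore *fD*.

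**False-positive rate.** SE = √(1/30 + 1/(30(1 − *f*))), and the rate is P(|Z + *fD*/SE| > 1.96).

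| *f* | Expected men removed | SE | *D* | Shift *fD* (SD) | False-positive rate |
|---|---|---|---|---|---|
| 5% | 1.5 | 0.262 | 0.5 | 0.025 | 0.051 |
| 5% | 1.5 | 0.262 | 1.0 | 0.05 | 0.054 |
| 10% | 3 | 0.265 | 0.5 | 0.05 | 0.054 |
| 10% | 3 | 0.265 | 1.0 | 0.10 | 0.066 |

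The last row in full: 0.10/0.265 = 0.377; upper tail 1 − Φ(1.96 − 0.377) = 0.0567; lower tail Φ(−1.96 − 0.377) = 0.0097; sum 0.066.

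**Chance that the rule acts at all.** At least one of 30 Exercise Group men is removed with probability 1 − 0.95^30 = 79% at *f* = 5%, and 1 − 0.90^30 = 96% at *f* = 10%.

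**Level against change.** If the failing men are lower by the same amount at every visit, their change equals that of the others. Then *D* = 0 and the shift in the Group x Time contrast is 0. Only a different course over time biases the planned test.

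**After the fix.** If all men are screened before allocation, or if every randomised man is followed and analysed as assigned, the *fD* term vanishes and the rate stays at the assumed 0.05.

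**The case against.** The case on the other side concerns the size and certainty of the harm, and much of it stands.

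- **Prior exclusions.** The exclusion criteria already remove, in both arms, severe cardiac disease, angina, uncontrolled hypertension and dysrhythmias, acute illness, recent pulmonary embolism and limiting neuromusculoskeletal disease. Few men may be left to fail the form. For contrast, *f* = 20% would give shifts of 0.10-0.20 SD and false-positive rates of 0.065-0.113, but nothing in the documents supports so high a rate. Control Group men are not unscreened either: they pass the nurse's check and miss only this form.
- **The planned test.** A reader might infer that the Exercise Group is bound to look fitter even if walking does nothing. The documents do not support this. A constant difference in level cancels in the Group x Time interaction. The direction is also open: men removed for acute symptoms might have recovered, and removing them would then count against exercise.
- **Recoverability.** A reader might also infer that no analysis could repair the loss. That goes too far. Baseline outcomes are collected before allocation, and the Endnote describes bone densitometry as standard care, so 12-month bone data may exist for excluded men. For the function and quality-of-life outcomes, however, follow-up comes only from the study sessions, and any repair would rest on untestable assumptions.
- **Discretion and pilot status.** The exclusion rule is mandatory once a contraindication is found, which limits discretion, though the open list leaves some. The design is called a pilot, but efficacy is a stated purpose and is tested.

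None of this changes the order of events or the fact that the rule applies to one arm.

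**Conclusion.** The point holds as a design defect: a stated exclusion after randomisation, in one arm only, applied by a person who knows the allocation. It can bias the Group x Time comparison if the removed men would have changed differently over 12 months.

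Its size and direction are not known. Assuming 30 per arm, 5-10% failing and a difference in change of 0.5-1 SD, the shift is about 0.025-0.10 SD and the false-positive rate about 0.051-0.066 against 0.05. It favours exercise if the removed men would have done worse, and exercise is disadvantaged if they would have done better.

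The reason to act is that the defect is plain in the text and cheap to remove before enrolment, not that a large bias has been shown.

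**What to change.** - Move the form to the baseline session, before GRA2 assigns the group, and give it to every consented man. Its clinical content and the referral to the family physician stay as they are. Exclude men who fail it at that point, before randomisation.
- State that any man found unable to exercise after randomisation stays in the study, is followed up as far as clinically permitted, and is analysed in his assigned group.

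**Cost.** A small amendment and one short form for each man who would become a control (about 30 if allocation is 1:1). No extra visit is needed, because GRA2 already meets every man for pedometer instruction before allocation. Men who would have failed in either arm now fail before randomisation, so some additional screen failures must be replaced. That puts some pressure on the plan to recruit 60 men in three months.
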